#### Uroflowmetry* (Flowtaker)

The patient is provided with the Flowtaker at the end of their invasive urodynamic visit. They will be provided with an information sheet on how to use this and instructed not to start this until given the green light to do so during their 3-day follow-up phone call. The flowmeter will be given with a prepaid envelope for the patient to post back to their urodynamic nurse for data upload.

#### GP summary report

Once the reference and index tests have taken place, results are compiled into a report which is provided to GPs, along with a summary of relevant NICE-recommended managements,^1^ to help inform management of the patient.

#### 6-month follow-up

A review of the patient’s medical notes will take place 6 months after the patient’s treatment and management decision with the GP. This will include any changes to treatment or management and whether they have since been referred to secondary care. Figure 1 depicts a flow diagram of the patient pathway.

**Figure 1 F1:**
[figure not shown]
Flow diagram depicting the patient pathway in the PriMUS study. GP, general practitioner; LUTS, lower urinary tract symptoms; PriMUS, PRImary care Management of lower Urinary tract Symptoms.

### Patient and Public Involvement

Patient and Public Involvement (PPI)
will be sought throughout the research process, from conceptualisation to
dissemination. PPI will contribute to the design, set up and management of the
study as well as the progress and conduct of the study as part of study
sub-groups. PPI representatives will also lead on dissemination activities to
study participants and the wider public.

### Safety and pharmacovigilance

Invasive urodynamics has the potential to cause adverse events. A medical doctor will be required on-site while the test is taking place. Due to a 5% risk of UTI,^3^ the urodynamic nurse will also provide the patients with a post-urodynamics debrief sheet following the test, informing them on the importance of drinking plenty of water for 24 hours following the test, how to identify signs of an infection and to seek medical care if they suspect they have one.

Adverse events will be captured by the urodynamic nurses, either during Study Visit Part B or during the 3-day follow-up phone call. For SAEs, an assessment of causality between the event and the study intervention, and the expectedness of the event, will be carried out by the Principle Investigator, or delegated urodynamic nurse, and then independently by a clinical reviewer. If the clinical reviewer classifies the event as *probably* or *definitely* caused by the intervention, it will be classified as a serious adverse reaction.

### Sample size

Sample size calculations were carried out separately for the model development and validation cohorts. For both, we used estimated prevalences for DO, BOO and DU of 57%, 31% and 16%, respectively, based on previous literature^4 5^ and clinical expertise.

#### Development cohort

The sample size for developing our predictive models was based on a rule of thumb suggesting that five events per variable are required.^6^ We chose a sample size of 350 to allow at least 11 variables in each model. This was driven by our lowest estimated prevalence of 16% for DU, giving 56 events (DU diagnoses).

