## Methods and analysis

### Study design

This is a prospective, diagnostic accuracy study involving the development and validation of a diagnostic tool. An internal pilot will assess primary care recruitment, acceptability of the reference test (invasive urodynamics) and data collection. Two cohorts of participants, one for development of the prototype diagnostic tool and other for validation, will undergo a series of index tests (see table 1) and the invasive reference standard (urodynamics) in approximately 90 GP practices across Newcastle upon Tyne, Wales and Bristol (a list of study sites can be found on ISRCTN). There will also be qualitative data collection to explore acceptability of the urodynamics test and develop management recommendations for the tool and for user-testing of the prototype (see table 2).

**Table 1 T1:** Index tests and input parameters that will be tested for use in the three logistic regression models

Test	Result	Input parameters that will be tested for use in the three logistic regression models (result or unit)
Relevant demographics	Age in years	Age (years)
Physical examination of abdomen	Bladder palpable/not palpable	N/A
Digital rectal examination	Prostate mild/moderate/severe enlargement Further assessment for prostate cancer required/not required	Prostate size (enlarged/not enlarged)
Prostate Specfic Antigen (PSA)	PSA value—established thresholds for further assessment for prostate cancer (typically >3 ng/mL) or benign enlargement (typically ≥1.5 ng/mL). For clinical decision support tool: continuous variable in ng/mL	PSA (ng/mL)
International Consultation on Incontinence Questionnaire Male Lower Urinary Tract Symptoms Short Form	Total score (0–52), voiding symptom score (0–20), storage symptom score (0–24). Individual symptom bother scores scored separately from symptom severity scores (0–130)	Storage/incontinence symptoms subscore Voiding symptoms subscore
International Prostate Symptom Score questionnaires	Total score (0–35)	Storage/incontinence symptoms subscore Voiding symptoms subscore
Bladder diary	Waking (day) time frequency, sleeping (night) time frequency, 24 hours voided volume, daytime voided volume, nocturnal voided volume, average volume voided each void, total urgency scores	Mean urgency score Mean 24 hours fluid intake (mL)

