### Index tests

Twelve potential parameters will be considered for the three logistic regression models. The investigations that provide these parameters are described in table 1.

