## Statistical analysis

Model development will be performed using results from the first 350 data sets, and external model validation performed using the subsequent 325 data sets.

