### Model development

Candidate predictor variables will be selected from those listed in table 1. Their selection has been informed by subject knowledge using literature review and expert judgement. As predictor distributions should be wide to facilitate reliable predictions, we will explore the distribution of each predictor prior to selection. Relationships between predictors will also be investigated; where indicated we will group related variables into a composite variable or exclude if highly correlated with other variables. Candidate predictors will not be selected based on univariable analyses; this practice is discouraged because predictors that may be important in a multivariable model can be missed and may also lead to overoptimistic models. Therefore, all selected candidate predictor variables will be included in the multivariable logistic regression models without evaluation of association between outcome and predictor and assessment of statistical significance. To gain maximum diagnostic information, continuous variables will not be categorised. We will allow for non-linearity by using a multivariable fractional polynomial approach to identify appropriate transformations. This may lead to the inclusion of non-linear terms in the models, thus increasing the number of variables in the models. Using multiply imputed data and Rubin’s rule, we will develop each model using backward elimination with a p value of 0.157 to select predictors for inclusion in each model. We chose this p value because it is known to be a good proxy for the Akaike information criterion approach. If the repeated use of Rubin’s rule is computationally challenging, we will use the approximation to Rubin’s rule recommended by Wood *et al*.^7^

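### The development cohort gives five events per variable for 11 variables in the DU model, but the article names 12 candidate parameters, tabulates 14 entries and allows further non-linear terms

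*Protocol article*

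**What the plan says.** All references are to the Protocol article.

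- **Sample size** uses "estimated prevalences for DO, BOO and DU of 57%, 31% and 16%, respectively".
- **Development cohort** sets the size "based on a rule of thumb suggesting that five events per variable are required" and concludes: "We chose a sample size of 350 to allow at least 11 variables in each model". DU, as the rarest condition, drives the number, with 56 expected cases.
- **Statistical analysis** confirms the denominator: "Model development will be performed using results from the first 350 data sets".
- **Index tests** gives the size of the candidate pool: "Twelve potential parameters will be considered for the three logistic regression models".
- **Table 1**, in its input-parameter column, has 14 entries. They are age, prostate size, PSA, storage and voiding subscores from each of two questionnaires, urgency score, fluid intake, maximum flow, voided volume, 24-hour frequency, nocturia and residual volume.
- **Model development** draws candidates from Table 1 and lets related variables be combined, or strongly correlated ones dropped, without looking at the outcome. It enters all selected candidates in the multivariable model and applies backward elimination at p = 0.157. On fractional polynomials it says: "This may lead to the inclusion of non-linear terms in the models, thus increasing the number of variables in the models".

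**The concern.** Three counts (11, 12 and 14) appear for what should be one quantity, and the sample size rests on the smallest. An events-per-variable rule guards against overfitting. When all candidates are entered and then eliminated backwards, the data are spent on the whole candidate set, not only on the predictors that survive. The number to hold against the 56 DU events is therefore the number of candidate parameters, with non-linear terms included.

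If that number exceeds 11, the design does not meet its own criterion for the condition that set the sample size. The DU model is then more exposed to overfitting than the sample size section implies. Predicting DU is part of the first primary objective.

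**Working it through.** **Inputs.** Development N = 350, five events per variable, and prevalences of 57% (DO), 31% (BOO) and 16% (DU), all from Sample size and Development cohort. Candidate counts are 12 (Index tests) and 14 (Table 1).

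**1. Reproduce the stated figure.** Events = 350 × 0.16 = 56. Variables allowed = 56 / 5 = 11.2, so 11. In reverse, 5 × 11 / 0.16 = 343.75, so 344 men, just under 350. The figure reproduces. The wording of at least 11 is true across the three models because DU is the limiting one; for DU itself, 11 is the ceiling.

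**2. Events per parameter, linear terms only.** The smaller outcome class is used: 56 events for DU, 350 × 0.31 = 108.5 events for BOO, and 350 × 0.43 = 150.5 non-events for DO.

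| Model | Smaller class | Parameters allowed at 5 | With 11 | With 12 | With 14 |
|---|---|---|---|---|---|
| DU | 56 | 11 | 5.09 | 4.67 | 4.00 |
| BOO | 108.5 | 21 | 9.86 | 9.04 | 7.75 |
| DO | 150.5 | 30 | 13.68 | 12.54 | 10.75 |

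Only DU falls short.

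**3. What the rule would need for DU.** With 12 parameters: 5 × 12 = 60 events, and 60 / 0.16 = 375 men. With 14: 5 × 14 = 70 events, and 70 / 0.16 = 437.5, so 438 men. Against 350, the gaps are 25 and 88 men.

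**4. Non-linear terms (illustrative ceiling).** The article does not state the fractional polynomial degree. Assume that every continuous or score predictor is charged 2 degrees of freedom (FP1) or 4 (FP2), and that prostate size, the one binary input, is charged 1.

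- 12 parameters: 1 + 11 × 2 = 23, or 1 + 11 × 4 = 45. DU events per degree of freedom: 56 / 23 = 2.4, or 56 / 45 = 1.2.
- 14 parameters: 1 + 13 × 2 = 27, or 1 + 13 × 4 = 53. DU events per degree of freedom: 56 / 27 = 2.1, or 56 / 53 = 1.1.

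**5. What this could mean for shrinkage (assumption, with range).** The Riley formula n = p / ((S − 1) ln(1 − R²cs / S)) was solved for the expected shrinkage S at n = 350. At 16% prevalence the maximum Cox–Snell R² is 0.585. The article gives no R², so Nagelkerke R² is assumed to lie between 0.15 and 0.40.

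| Candidate df | S at R² 0.15 | S at R² 0.20 | S at R² 0.40 |
|---|---|---|---|
| 11 | 0.75 | 0.80 | 0.90 |
| 12 | 0.73 | 0.79 | 0.89 |
| 14 | 0.70 | 0.76 | 0.87 |
| 27 | 0.55 | 0.63 | 0.78 |
| 53 | 0.40 | 0.47 | 0.66 |

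Going from 11 to 14 linear terms costs little. Unrestricted non-linear terms could cost much more.

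**The case against.** The case for the plan has real weight.

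- **The sample size section speaks of variables in each model, not of candidates.** This is so, and the source of the rule is not at hand. But Model development fits all selected candidates together before eliminating any, so the full set does form a model on 56 events. A shorter final model does not undo that.
- **Table 1's 14 may really be 12.** The two questionnaire rows carry identical subscore entries. Counted once, the total is 12 and agrees with Index tests. This reading is plausible, and the figures for 14 should be held loosely. It still leaves 12 against 11.
- **The pool may be reduced before modelling.** Dropping or merging one of 12, or three of 14, would meet the rule with linear terms. The article permits this but ties it to no limit.
- **The gap at 12 is small.** It is 56 against 60 events under a rule of thumb, and it closes if DU prevalence is 60 / 350 = 17.1%. The article itself lists uncertain prevalence as a limitation. This stands.
- **The harm is already addressed.** Model validation repeats variable selection within bootstrap samples, applies the optimism-adjusted slope as a shrinkage factor, and then tests the models in a separate cohort of 325. These steps measure and limit overfitting; they do not make the stated criterion true.

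A reader might go further and infer that the sample size arithmetic is wrong, or that the DU model is bound to be overfitted with only one or two events per parameter. The article supports neither. The arithmetic reproduces, the low figures are ceilings under an unstated polynomial degree, and the text says only that non-linear terms may enter. At an assumed R² of 0.20, most of the expected shrinkage is already present at 11 parameters, where the rule is met.

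**Conclusion.** The concern holds as an inconsistency in the basis of the development sample size, confined to DU. On the article's own prevalence, the five-events rule is met for 11 parameters and missed for the counts given elsewhere: 4.7 with 12 and 4.0 with 14. Any fractional polynomial terms lower this further, to about 1 to 2 in the illustrative worst case. BOO and DO are unaffected.

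The conclusion rests on counting candidate parameters rather than retained ones, on 16% DU prevalence, and on the planned reduction step having no numerical target. With 12 linear parameters the shortfall is minor; the open question is mainly how many non-linear terms will be added. Given the safeguards already planned, this is a should-fix point: it corrects a figure on which the sample size relies and does not put the study's design in doubt.

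**What to change.** State one candidate count, the same in Table 1, Index tests and Development cohort. Count it in parameters, non-linear terms included, and say whether the two questionnaires' subscores are alternatives or are all candidates. Then choose one of two routes.

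(a) Before any outcome data are examined, use the grouping or exclusion step already in Model development to hold the DU candidates to 11 parameters. For example, keep one questionnaire's subscores (14 to 12) and merge or drop one further correlated variable (12 to 11). Any non-linear term must fit inside that budget, so each one needs room made elsewhere. Strictly linear terms for DU are not required; that would trade overfitting against misspecification.

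(b) Keep the fuller set and restate the DU events per variable as 4.0 to 4.7 before non-linear terms and lower with them, pointing to the planned shrinkage and validation as the safeguard.

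The cost is a change of wording, plus slightly less flexibility in the DU model under (a) or a less favourable stated figure under (b). Neither route needs more men. BOO and DO can keep the full set, with room for some non-linear terms within about 21 and 30 parameters.

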#### Validation cohort

The sample size for the validation cohort was chosen to ensure that estimates of test accuracy are made with adequate precision. We deem sensitivity and specificity of 75% to be the minimum clinically useful performance. We chose a sample size of 325, giving estimates of sensitivity of 75% to within 8%, 10% and 14% for DO, BOO and DU respectively, based on ‘positive’ samples of 185, 101 and 52, and estimates of specificity of 75% to within 8%, 7% and 6%, based on ‘negative’ samples of 140, 224 and 273. Better sensitivity and specificity will give narrower CIs.

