We will externally validate the models and calculate performance statistics (c-index and calibration slope) using the validation cohort. The value for the calibration slope should ideally be one signifying perfect agreement between the predicted probabilities and the observed probabilities. A calibration slope <1 indicates that a model overpredicts while a calibration slope >1 indicates underprediction. From the qualitative research, we will ascertain distributions of probability (risk) thresholds for clinical usefulness of the prediction in guiding treatment of each condition. The sensitivity and specificity (and their corresponding 95% CIs) will be calculated for these risk thresholds and plotted on an ROC plot for each model.

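### The 8% precision margin for DO sensitivity (185 positives) does not fit the other five validation margins; on the bases that give those five it is 7%

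*Protocol article*

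**What the plan says.** The Sample size section of the Protocol article assumes "estimated prevalences for DO, BOO and DU of 57%, 31% and 16%, respectively". Under Validation cohort it sets the target, "We deem sensitivity and specificity of 75% to be the minimum clinically useful performance", and then the size: "We chose a sample size of 325". The sensitivity margins are given as "giving estimates of sensitivity of 75% to within 8%, 10% and 14% for DO, BOO and DU respectively". The same sentence reports the counts behind them: "based on ‘positive’ samples of 185, 101 and 52". For specificity the text has "estimates of specificity of 75% to within 8%, 7% and 6" (the last figure is also a percentage). The counts used there appear as "based on ‘negative’ samples of 140, 224 and 273".

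That paragraph names neither a confidence level nor an interval method. The level can be taken from the Model validation section: "The sensitivity and specificity (and their corresponding 95% CIs) will be calculated for these risk thresholds".

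**The concern.** DO is given the same 8% margin for sensitivity and for specificity, both at an assumed 75%. One rests on 185 men and the other on 140. A third more men (185/140 = 1.32) should give a visibly narrower margin, so the two figures cannot come from one rule.

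A reader who tries to check the sentence also meets a second difficulty. The usual 95% formula at 75% returns none of the six figures to the nearest point, so it is unclear what being within 14% means for DU.

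These margins are the only justification the article gives for the validation cohort, which provides the primary outcome (sensitivity and specificity). They should be reproducible and consistent with one another.

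**Working it through.** **Inputs.** n = 325; prevalences 57%, 31% and 16%; accuracy 75%; two-sided 95% (z = 1.96), the level being taken from Model validation.

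**Counts.** 325 × 0.57 = 185.25, 325 × 0.31 = 100.75 and 325 × 0.16 = 52, which gives 185, 101 and 52 positives. Subtracting from 325 gives 140, 224 and 273 negatives. All six counts agree with the article.

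**Margins, in percentage points.**

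- A: Wald at 75%, 1.96 × √(0.1875/n).
- B: Wald at p = 0.5, 1.96 × 0.5/√n.
- C: 75 minus the Wilson lower limit, where the limit is [p + z²/2n − z√(p(1−p)/n + z²/4n²)] / (1 + z²/n) with p = 0.75.
- D: 75 minus the exact (Clopper-Pearson) lower limit, taking 0.75n successes.

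| | n | Stated | A | B | C | D |
|---|---|---|---|---|---|---|
| DO sensitivity | 185 | 8 | 6.24 | 7.20 | 6.71 | 6.88 |
| BOO sensitivity | 101 | 10 | 8.44 | 9.75 | 9.26 | 9.60 |
| DU sensitivity | 52 | 14 | 11.77 | 13.59 | 13.21 | 13.95 |
| DO specificity | 140 | 8 | 7.17 | 8.28 | 7.78 | 8.02 |
| BOO specificity | 224 | 7 | 5.67 | 6.55 | 6.06 | 6.20 |
| DU specificity | 273 | 6 | 5.14 | 5.93 | 5.46 | 5.57 |

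Worked example of C for n = 185: (0.75 + 0.01038 − 0.06326)/1.02077 = 0.6829, and 75 − 68.29 = 6.71.

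**Comparison with the stated 8, 10, 14; 8, 7, 6.**

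- A to the nearest point: 6, 8, 12; 7, 6, 5. None match. Rounded up: 7, 9, 12; 8, 6, 6. Two match.
- B to the nearest point: 7, 10, 14; 8, 7, 6. Five match; only DO sensitivity fails.
- C rounded up: 7, 10, 14; 8, 7, 6. Five match; only DO sensitivity fails.
- D to the nearest point: 7, 10, 14; 8, 6, 6. Rounded up: 7, 10, 14; 9, 7, 6. Four match either way.

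**Can 185 and 140 men share a margin of 8?** For any margin proportional to 1/√n, the ratio is √(185/140) = 1.15.

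- Nearest point: if n = 185 is at least 7.5, then n = 140 is at least 8.6, which is 9.
- Rounding up: if n = 185 is above 7, then n = 140 is above 8.05, which is 9.
- Rounding down: if n = 185 is at least 8, then n = 140 is at least 9.2, which is 9 or more.

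No rounding rule gives 8 for both.

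**Men needed for 8 points.** 1.96² × 0.1875/0.08² gives about 113 at 75%, and 1.96² × 0.25/0.08² gives about 150 at p = 0.5. Neither is 185.

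**The case against.** **All six margins are wrong.** A reader might infer this because none equals the Wald half-width at 75% to the nearest point. The article does not say it used that formula. Five figures are defensible as Wilson lower arms rounded up, or as worst-case margins at p = 0.5. The text does not show which, and leaving the interval method to a fuller document is not a fault.

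**A margin of 8% is still true as a bound.** The DO sensitivity margins of 6.2, 6.7, 6.9 and 7.2 all lie within 8, so the cohort is not made to look more precise than it is. That stands, and it limits the importance of the point. It does not make the sentence consistent: the other five figures are tight to the point on bases B and C, and this one is not.

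**All six can be recovered.** Round successes down to whole men (138, 75, 39; 105, 168, 204), take Wilson limits to one decimal, measure their distance from 75 and round up. This gives 8, 10, 14; 8, 7, 6. But the distances are measured from 75, not from the proportion that each count implies (138/185 = 74.6%). It also needs the limits cut to one decimal before rounding up, since the BOO distance is otherwise 10.05 and rounds up to 11. That is too contrived to rescue the text.

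**The slip could be in DO specificity instead.** Basis B rounded up throughout gives 8, 10, 14; 9, 7, 6, so DO specificity would be the misfit, at 9. This cannot be excluded from the article alone. The 7% reading is preferred because B with ordinary rounding and C with rounding up both lead to it. On either account the two 8s cannot both stand.

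**Conclusion.** The point holds as a small internal inconsistency. With 185 positives, the DO sensitivity margin is 7% (7.2 or 6.7 points) on the two bases that give the other five figures, not 8%. On these bases the error overstates imprecision by about one point. It rests on a two-sided 95% level, on 75% taken as an exact proportion, and on one method and rounding rule applied to all six.

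The stated margins are not symmetric half-widths at 75%. For DU sensitivity the 95% interval at 75% is 61.1% to 86.0% (exact) or 61.8% to 84.8% (Wilson). The 14 therefore fits the longer, lower arm or a worst-case figure, not plus or minus 14.

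A reader might go further and infer that the validation cohort is wrongly sized. The documents do not support that: the counts are right, the DO sensitivity figure errs on the cautious side, and neither 325 nor 880 moves.

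**What to change.** Edit the one sentence under Validation cohort in either of two ways.

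1. Keep the margins, change DO sensitivity to 7%, and state the basis: 95%, and either worst-case half-widths at p = 0.5 or the distance from 75% to the lower limit. The sponsor should check this against the original calculation. If that calculation used p = 0.5 rounded up, DO specificity is the figure to change, to 9%.
2. Replace all six with 95% intervals at 75%, and name the method. Exact intervals are: sensitivity DO 68–81%, BOO 65–83%, DU 61–86%; specificity DO 67–82%, BOO 69–81%, DU 69–80%.

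The second is clearer, because it removes the question of symmetry. Either costs one sentence, with no change to sample size, recruitment or analysis.
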